## 5.4 Administration of Study Intervention

Prior to implementing the SEL curriculum, facilitators in the active intervention arm will require training. Training will take place after randomization occurs. Facilitators in the intervention arm will receive training at an agreed upon date in fall 2024. Initial training will be delivered in-person. Facilitators will not be compensated for their time in the training, but will be offered an honorarium to complete post-training questionnaires. Facilitators in the intervention arm only will have the opportunity for continued training in our weekly coaching sessions.

Once facilitators receive training, they will be able to implement the SEL lesson plan topics into their existing program activities twice each week at the timelines allotted for the intervention (fall 2024).We are asking facilitators in the intervention arm to complete weekly fidelity checklists to monitor adherence and adaptations to the curriculum and will host weekly coaching sessions with facilitators to support their administration of the SEL curriculum intervention.

## 5.5 Participant Compliance Monitoring

Facilitators in the intervention arm will be asked to complete weekly fidelity checklists which include a question assessing whether youth are engaged in the SEL lessons. We have structured weekly coaching sessions with facilitators (in the intervention arm) to discuss any challenges they may be having with unengaged youth.

## 5.6 Concomitant Therapy

Not applicable

## 5.7 Packaging

Not applicable

## 5.8 Blinding of Study Intervention

Not applicable

## 5.9 Receiving, Storage, Dispensing and Return

### 5.9.1 Receipt of Study Intervention Supplies

Not applicable

### 5.9.2 Dispensing of Study Intervention

Not applicable

### 5.9.3 Return or Destruction of Study Intervention

Not applicable

# 6 RESEARCH PROCEDURES

## 6.1 Research Visits

- Baseline Visit: Collection of pre-SEL curriculum implementation data
  - Youth and staff from both active intervention and usual programming control arms will be asked to participate in this data collection time point.
  - Youth questionnaires:
    - Demographic questions (researcher-created)
    - SSIS-SEL Brief Scale (Elliot et al., 2020)
    - KIDSCREEN (Child Public Health, 2024)
    - CD-RISC 10 (2007)

Procedure of youth data collection: Two CAMH research staff who meet the requirements of delivering consent procedures (e.g., cannot be an undergraduate student, must have proper training) will go to each of the 20 sites and (1) verbally go through the consent procedure with each class, (2) after the consent form is read to the class, CAMH research staff will check-in with each youth to ask them if they have any questions they can clarify about consent, (3) ask each youth to sign the consent form should they wish to proceed with participating in the completing the study measures (youth will sign these on tablets provided by CAMH, (4) data collection will begin, CAMH personnel will read aloud each question to the class while youth will record their answers on REDCap which will be set up on the tablet, (5) collect the tablets when everyone is finished, (6) provide a pizza party honorarium for their participation (every youth, regardless of whether they participate in the study or not, will be able to participate in the pizza party).

- - Staff questionnaires:
    - Demographic questions (researcher-created)
    - SSIS-SEL Brief Scale (Elliot et al., 2020)

KIDSCREEN 10 (Child Public Health, 2024Procedure of staff consent: Two CAMH research staff who meet the requirements of delivering consent procedures (e.g., cannot be an undergraduate student, must have proper training) will go to each of the 20 sites and (1) verbally go through the consent procedure with each facilitator, (2) ask each facilitator to sign the consent form via REDCap if they agree to participate, and (3) email each facilitator a signed copy of their completed consent form, (3) once consent is received from each staff member, we will email them a secure link to complete their survey online via REDCap, and (4) they will receive a $30 e-gift card of their choice for participating in the survey.

- 1. The pre and post measures will not contain any identifying information, such as names. Each youth participant will be assigned a study ID at the beginning of the study, which will be associated with their REDCap surveys. Youth and facilitators will be sent a unique link for each youth, where youth and facilitators will complete surveys. Study IDs will be linked to youth participant demographic information in a separate decoder document to which only research staff will have access. The file will be password-protected and saved on the CAMH network. Facilitators will be provided with information that links each youth ID to a youth’s name in a Word document via a secure data transfer. No other information about the youth apart from their ID and name will be part of this data. Facilitators will be able to save this document for use while they are completing youth questionnaires, but will be told to delete the file when they are finished completing the youth surveys. Facilitators will only complete surveys for youth aged 11-14 years registered in their site who have consented to participating in the study.
- Weekly Fidelity Checklists, Data Collection
  - Staff in the active intervention arm will be asked to complete a weekly fidelity checklist for the duration of the SEL curriculum implementation.

Procedure of staff data collection: Automatic invites will be set up on REDCap and sent to facilitators to complete the weekly fidelity checklist online via REDCap. The honorarium for completing the weekly fidelity checklist is a monthly draw for, for 16 weeks, for 2 X $50 e-gift card of choice.

- Weekly Coaching Sessions (this is offered to staff to support their implementation of the EMPOWER SEL curriculum)
  - There will be 2 weekly coaching sessions (with 10 facilitators in each group) held that staff in the active intervention arm will be asked to attend. These coaching sessions will be scheduled online via Webex. Notes containing no personal identifying information will be taken to document these meetings. Should facilitators be unable to attend, they will be sent the meeting notes to review via email. The weekly coaching sessions are held to maintain fidelity to the intervention and provide facilitators with ongoing support and guidance. Meeting notes are taken so that facilitators and program staff can refer back to information that was discussed. As such, if a facilitator misses a meeting they will be sent meeting notes in order to provide them with information about discussion and support fidelity. There is no honorarium for the weekly coaching sessions. Staff will be sent a Webex meeting invite weekly for a 30-minute session.
- Monthly Feasibility Measures, Data Collection
  - Staff in the active intervention arm will be asked to complete three feasibility measures every 4 weeks, after each SEL domain has been taught.
    - Feasibility of Intervention Measure (Weiner et al., 2017)
    - Acceptability of Intervention Measure (Weiner et al., 2017)
    - Intervention Appropriateness Measure (Weiner et al., 2017)

Procedure of staff data collection: We will email staff a secure link to complete the survey online via REDCap. The honorarium for completing the feasibility measures each month is a monthly draw for, for 16 weeks, for 2 X $50 e-gift card of choice.

- Post-SEL curriculum implementation: Data Collection
  - Youth and staff from both active intervention and usual programming control arms will be asked to participate in this data collection time point.
  - Youth questionnaires:
    - SSIS-SEL Brief Scale (Elliot et al., 2020)
    - KIDSCREEN (Child Public Health, 2024)
    - CD-RISC 10 (2007)

Procedure of youth data collection: Two CAMH research staff who meet the requirements of delivering consent procedures (e.g., cannot be an undergraduate student, must have proper training) will go to each of the 20 sites and (1) distribute tablets to each youth, (2) read aloud each question to the class while youth will record their answers on REDCap which will be set up on the tablet, (3) collect the tablets when everyone is finished, (4) provide a pizza party honorarium for their participation (every youth, regardless of whether they participate in the study or not, will be able to participate in the pizza party).

- - Staff questionnaires:
    - SSIS-SEL Brief Scale (Elliot et al., 2020)
    - KIDSCREEN 10 (Child Public Health, 2024)

Qualitative Questions (researcher created) Procedure of staff data collection: We will email staff a secure link to complete the survey online via REDCap. They will receive a $30 e-gift card of their choice for participating in the survey. The pre and post measures will not contain any identifying information, such as names. Each youth participant will be assigned a study ID at the beginning of the study, which will be associated with their REDCap surveys. Youth and facilitators will be sent a unique link for each youth, where youth and facilitators will complete surveys. Study IDs will be linked to youth participant demographic information in a separate decoder document to which only research staff will have access. The file will be password-protected and saved on the CAMH network. Facilitators will be provided with information that links each youth ID to a youth’s name via a secure data transfer. No other information about the youth apart from their ID and name will be part of this data. Facilitators will only complete surveys for youth aged 11-14 years registered in their site who have consented to participating in the study.

Procedure of parent data collection: Beyond 3:30 administration will identify at least 1 parent from each of the intervention arm sites they feel would be interested in participating in a 30-minute interview, thus we are adopting a convenience sampling approach. More than 1 parent representing more than one youth can participate. We are aiming to interview at least 10 parents. Beyond 3:30 staff will reach out to all parents in an email with an invitation to participate, in order to identify at least 1 parent at each of the 10 sites.

- - Beyond 3:30 administration will email parents an invitation to participate in a 30-minute study with a copy of the informed consent form attached. If the caregiver is interested in participating, a member of the study team will call the caregiver to go over the consent form. If the caregiver agrees to participate in the study, a virtual interview via Webex will be scheduled. During this interview, a member of the study team will ask the caregiver about their child’s social emotional skills. . Caregivers will receive a $15 gift card of their choice for participating in the interview.

## 6.2 Schedule of Events

| **Procedures** | Two weeks pre- SEL curriculum implementation | Week  1 | Week  2 | Week  3 | Week  4 | Week  5 | Week  6 | Week  7 | Week  8 | Week  9 | Week  10 | Week  11 | Week  12 | Week  13 | Week  14 | Week  15 | Week  16 | Two weeks post-SEL curriculum implementation |
| --- | --- | --- | --- | --- | --- | --- | --- | --- | --- | --- | --- | --- | --- | --- | --- | --- | --- | --- |
| **Pre-SEL Implementation Data Collection (participants in active and usual programming arms)** |  |  |  |  |  |  |  |  |  |  |  |  |  |  |  |  |  |  |
| Youth Consent | X |  |  |  |  |  |  |  |  |  |  |  |  |  |  |  |  |  |
| Facilitator Consent | X |  |  |  |  |  |  |  |  |  |  |  |  |  |  |  |  |  |
| Administration of Youth Survey | X |  |  |  |  |  |  |  |  |  |  |  |  |  |  |  |  |  |
| Administration of Staff Survey | X |  |  |  |  |  |  |  |  |  |  |  |  |  |  |  |  |  |
| **Administration of the SEL Curriculum (active intervention arm)** |  | X | X | X | X | X | X | X | X | X | X | X | X | X | X | X | X |  |
| **Fidelity Checklists (facilitators in active intervention arm)** |  | X | X | X | X | X | X | X | X | X | X | X | X | X | X | X | X |  |
| **Coaching Sessions (facilitators in active intervention arm)** |  | X | X | X | X | X | X | X | X | X | X | X | X | X | X | X | X |  |
| **Feasibility Measures for each SEL domain (facilitators in active intervention arm)** |  |  |  |  | X |  |  |  | X |  |  |  | X |  |  |  | X |  |
| **Post -SEL Implementation Data Collection (participants in active and usual programming arms)** |  |  |  |  |  |  |  |  |  |  |  |  |  |  |  |  |  | X |
| **Administration of Youth Survey** |  |  |  |  |  |  |  |  |  |  |  |  |  |  |  |  |  | X |
| Administration of Staff Survey |  |  |  |  |  |  |  |  |  |  |  |  |  |  |  |  |  | X |
| Parent/Caregiver Consent |  |  |  |  |  |  |  |  |  |  |  |  |  |  |  |  |  | X |
| Parent/Caregiver Interview |  |  |  |  |  |  |  |  |  |  |  |  |  |  |  |  |  | X |
|  |  |  |  |  |  |  |  |  |  |  |  |  |  |  |  |  |  |  |
|  |  |  |  |  |  |  |  |  |  |  |  |  |  |  |  |  |  |  |

# 7.0 STATISTICAL PLAN

## 7.1 Sample Size Determination

**Sample size considerations**

Sample size and power calculations were performed using Power Analysis and Sample Size Software (PASS; 2024).

Co-primary endpoint 1: Feasibility

Feasibility will be assessed by facilitators in the active intervention arm. We expect N=20 facilitators in total (10 active sites x 2 facilitators per site). A sample size of 20 facilitators achieves an exact binomial 95% confidence interval width = 42.3% for co-primary endpoint 1, assuming the intervention is feasible for 14 out of 20 (70%) facilitators.

Co-primary endpoint 2: Social emotional learning

A sample size of 20 clusters (10 active, 10 usual programming) with an average of 20 youth per cluster achieves 89% power (α=5%) to detect a small to medium effect size of 0.35 between arms in the primary endpoint. We assume the coeffient of variation for the cluster sizes is assumed to be 0.25, and the intracluster correlation (ICC) is 0.01.

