## 7.2 Statistical Methods

1. Co-primary Objectives: Feasibility

   Acceptability, Feasibility, and Appropriateness of Intervention Measures: Descriptive statistics will be used to summarize acceptability, feasibility, and appropriateness of intervention measures. Frequencies and proportions will summarize categorical measures; means, medians, standard deviations and ranges will summarize continuous measures.

The frequency and proportion of facilitators and youth who “completely agree” or “agree” that the SEL curriculum is feasible, acceptable, and appropriate will be calculated, along with exact binomial 95% confidence intervals. We’ve set our progression criteria threshold to 70% for feasibility measures. This means that 70% of facilitators and youth “completely agree” or “agree” that the SEL curriculum is feasible, acceptable, and appropriate. We use a traffic light approach (Mellor et al., 2021) where meeting the set threshold equates to a green light and that the curriculum can proceed into its next phases of testing. Changes to the SEL curriculum are required should the threshold not be met (50%-60% = yellow light, or under 50% = red light). In these cases, a consensus meeting with the EMPOWER collaborative (partners [beyond 3:30 and VOS] and staff, youth, and caregiver advisors) will follow to determine necessary revisions and determine the best way to move forward.

Fidelity checklists: Each of the constructs within the fidelity checklist are measured in one-item and are descriptive in nature. They will be analyzed as such.

1. Co-primary Objectives: Social-Emotional Learning
2. SSIS-SEL Brief Scale

The unit of analysis for the primary comparison is individual youth. Linear mixed models will be used to compare pre-post intervention SSIS-SEL scores between groups assuming the fixed effects of treatment group (EMPOWER vs. Usual Programming), time (0 and 18 weeks post-initiation of intervention, and treatment-by-time interaction. To account for repeated measures, random effects of site and youth will be included in the model.

1. Secondary Objectives (secondary)
2. KIDSCREEN and CD-RISC 10 Measures

A similar statistical approach as for co-primary endpoint 2 (SEL) will be used to compare secondary endpoints between arms.

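### The 89% power for co-primary endpoint 2 rests on a large-sample reference distribution; with 20 randomised sites (18 degrees of freedom) the protocol's own inputs give about 85%

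*Protocol*

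**What the plan says.** Section 7.1 gives the design as "A sample size of 20 clusters (10 active, 10 usual programming) with an average of 20 youth per cluster" and states that it "achieves 89% power (α=5%) to detect a small to medium effect size of 0.35 between arms in the primary endpoint". Its other assumptions are the "coeffient of variation for the cluster sizes is assumed to be 0.25" and that "the intracluster correlation (ICC) is 0.01". The same calculation appears in the Clinical Trial Summary under Statistical Methodology. PASS 2024 is named as the software. The PASS procedure, the sidedness of the test and the reference distribution are not given.

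Section 5.3 randomises sites, 1:1. Section 7.2 says "The unit of analysis for the primary comparison is individual youth" and plans a linear mixed model with treatment, time and treatment-by-time as fixed effects and with random effects of site and youth. It gives no rule for degrees of freedom.

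**The concern.** The arms differ by site, so the evidence on the treatment effect comes from ten sites against ten. A test that estimates its error from variation between sites has 20 − 2 = 18 degrees of freedom and a two-sided 5% critical value of 2.10. The large-sample value is 1.96, or 1.97 with 398 degrees of freedom. The design effect in the calculation allows for correlation within sites. It does not allow for the small number of sites from which that correlation is estimated.

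The power of the efficacy co-primary is therefore stated too high for a site-level test. The choice can also decide a borderline result: a test statistic between about 1.97 and 2.10 is significant on one basis and not on the other.

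**Working it through.** **Inputs (section 7.1):** k = 10 sites per arm, mean size m = 20, CV = 0.25, ICC = 0.01, standardised effect 0.35, α = 5%. A two-sided test is assumed, because a one-sided 5% test gives 93.9% (normal) or 92.3% (18 df) and neither matches 89%.

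**Step 1, design effect.** 1 + ((CV² + 1)·m − 1)·ICC = 1 + (1.0625 × 20 − 1) × 0.01 = 1.2025.

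**Step 2, standard error and noncentrality.** There are 10 × 20 = 200 youth per arm. SE = √(2 × 1.2025 / 200) = 0.1097. Noncentrality = 0.35 / 0.1097 = 3.19.

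**Step 3, power at two-sided 5%.**

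| Reference distribution | Critical value | Power |
|---|---|---|
| Normal | 1.960 | 89.1% |
| t, 398 df (400 youth − 2) | 1.966 | 89.0% |
| t, 18 df (20 sites − 2) | 2.101 | 85.5% |
| t, 16 df (two site-level randomisation covariates also fitted) | 2.120 | 85.0% |

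The first two rows reproduce the stated 89%. The 18-df row does not, and it stays between 85.4% and 85.8% when the cluster-size correction is varied or set to zero.

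**Step 4, detectable effect.** On 18 df, 89% power needs an effect of 0.370. At 0.35 it would take 11 sites per arm (20 df, 88.9%), but the programme has only 20 sites and all are already in the trial.

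**Step 5, type I error.** On a t distribution with 18 df, a cut-off of 1.96 has a two-sided tail area of 6.6%, and 1.966 has 6.5%. That applies to a test built on site means. For a random-site model fitted by REML (simulated on post scores only, unequal site sizes, site variance held at or above zero):

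| ICC | Size, cut-off 1.96 | Size, cut-off 2.10 | Power, cut-off 1.96 | Power, cut-off 2.10 |
|---|---|---|---|---|
| 0.01 (protocol) | 5.0% | 3.6% | 87.8% | 84.7% |
| 0.05 (assumed) | 6.7% | 5.1% | 70.2% | 65.3% |

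At ICC 0.01 the site variance is estimated as zero in about a third of simulated trials, which keeps the size near 5%.

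**Step 6, the pre-post model.** If the random effects in section 7.2 are intercepts only (the section does not say), the site intercept largely cancels from the treatment-by-time contrast, which becomes a youth-level comparison of change. If sites do not differ in mean change, that test has the right size: simulation gives about 5%. If they do, with an assumed ICC of 0.01 in the change score, the test ignores a design effect of 1.2025. Its size is then 2·P(Z > 1.96/√1.2025) = 2·P(Z > 1.787) = 7.4%. Simulation gives 7.2 to 7.3%, against about 5% for a test of site means on 18 df.

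**The case against.** The strongest objection is that nothing was miscalculated. The 89% follows from the stated inputs by a standard design-effect formula. That is right, and the point should not be called an arithmetic slip. Nor do the documents show that youth-level degrees of freedom were used, since the ordinary normal approximation gives the same figure. Naming youth as the unit of analysis is no evidence of it either, because the same paragraph of section 7.2 includes a random site effect.

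A reader might also infer that the planned test really runs at 6.5%. The documents do not support this. They fix no critical value, and a power approximation does not set the size of the eventual test. The 6.5% belongs to a site-mean t test read against a large-sample cut-off. The REML random-site model at the protocol's ICC has size of about 5%, rising to about 6.5 to 6.7% only at a larger ICC such as the assumed 0.05. With the 1.96 cut-off that model has 87.8% power at ICC 0.01, only about one point below the stated figure.

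Two further objections carry weight. A degrees-of-freedom method is commonly left to the SAP, so its absence from section 7.2 is not an error. The loss is also modest: power stays above 80%, and uncertainty in the ICC and effect size may matter more. What remains is that section 7.1 states a figure, and that figure does not hold for a test that respects the number of randomised units.

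**Conclusion.** The concern holds as a small-sample limitation of the stated power. On the protocol's own inputs, a two-sided 5% test on 18 site-level degrees of freedom has about 85% power for an effect of 0.35, not 89%, and 89% power corresponds to an effect of about 0.37. This needs no assumption about consent, attrition or a different ICC. It does rest on reading α as two-sided and on testing the treatment effect against between-site variation.

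No inflation of type I error is established for the planned analysis. That would depend on a larger ICC, or on site differences in change that the fitted model leaves out, and the protocol settles neither. The consequence is limited: a headline operating characteristic needs correcting, and the trial's viability is not in doubt.

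**What to change.** In section 7.1 and the Clinical Trial Summary, keep the inputs and restate the result as: *about 85% power for an effect of 0.35, two-sided α = 5%, 18 site-level degrees of freedom*.

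In section 7.2, state that the SSIS-SEL treatment effect, meaning the treatment-by-time contrast, is tested two-sided at 5% with site-based inference. Examples are between-within degrees of freedom set to 18, or a site-level analysis of change. Do not rely on Kenward-Roger with intercept-only random effects to produce this: the site intercept largely cancels from that contrast, so the method would return roughly youth-level degrees of freedom.

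The cost is a few sentences of wording and an analysis setting, with no change in enrolment. The stated power falls by about 4 points after rounding. If the ICC really is 0.01, the test is slightly conservative: 3.6% size in the REML simulation with the 18-df cut-off.

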## 7.2 Statistical Methods

1. Co-primary Objectives: Feasibility

   Acceptability, Feasibility, and Appropriateness of Intervention Measures: Descriptive statistics will be used to summarize acceptability, feasibility, and appropriateness of intervention measures. Frequencies and proportions will summarize categorical measures; means, medians, standard deviations and ranges will summarize continuous measures.

The frequency and proportion of facilitators and youth who “completely agree” or “agree” that the SEL curriculum is feasible, acceptable, and appropriate will be calculated, along with exact binomial 95% confidence intervals. We’ve set our progression criteria threshold to 70% for feasibility measures. This means that 70% of facilitators and youth “completely agree” or “agree” that the SEL curriculum is feasible, acceptable, and appropriate. We use a traffic light approach (Mellor et al., 2021) where meeting the set threshold equates to a green light and that the curriculum can proceed into its next phases of testing. Changes to the SEL curriculum are required should the threshold not be met (50%-60% = yellow light, or under 50% = red light). In these cases, a consensus meeting with the EMPOWER collaborative (partners [beyond 3:30 and VOS] and staff, youth, and caregiver advisors) will follow to determine necessary revisions and determine the best way to move forward.

Fidelity checklists: Each of the constructs within the fidelity checklist are measured in one-item and are descriptive in nature. They will be analyzed as such.

1. Co-primary Objectives: Social-Emotional Learning
2. SSIS-SEL Brief Scale

The unit of analysis for the primary comparison is individual youth. Linear mixed models will be used to compare pre-post intervention SSIS-SEL scores between groups assuming the fixed effects of treatment group (EMPOWER vs. Usual Programming), time (0 and 18 weeks post-initiation of intervention, and treatment-by-time interaction. To account for repeated measures, random effects of site and youth will be included in the model.

1. Secondary Objectives (secondary)
2. KIDSCREEN and CD-RISC 10 Measures

A similar statistical approach as for co-primary endpoint 2 (SEL) will be used to compare secondary endpoints between arms.

